**RATIONALE**

*S. pneumoniae* is frequently isolated from nasal swabs of healthy subjects, but it can also cause severe diseases (pneumonia, bacteraemia, meningitis and sepsis).HIV-infected subjects are more sensitive to invasive diseases and recurrent infection than the general population. Nasal carriage is the main pathogenetic feature for invasive disease: bacteraemia is more frequent in carriers, HIV+ patients are constantly colonized by the same pneumococcal strain and their nasopharyngeal isolates have features similar to subsequent invasive strains. A 23-valent polysaccharide vaccine (PPV23) has long been available and recommended in the HIV+ population as prophylaxis for invasive disease. Studies regarding efficacy of PPV23 in HIV+ are controversial and highlight that immune response induced by PPV23 in HIV+ is poor and an hyporesponsiveness to repeated polysaccaridic antigens stimulation can occur. Moreover, PPV23 seems not to affect pneumococcal carriage status and could lead to emergence of non-vaccine serotypes. The conjugation of pneumococcal capsular polysaccharides to carrier proteins results in an improved T-cell dependent immune response, characterized by increased antibody concentrations and induction of T and B memory cells, with a demonstrated higher efficacy in children. A heptavalent vaccine conjugated with diphtheria toxoid (PCV7) is approved in Europe since 2001 and is effective in reducing incidence of invasive disease by vaccine serotypes (4, 6B, 9V, 14, 18C, 19F, 23F), in both children and adults, due to effect of herd immunity. A PCV13 formulation has recently been developed, covering PCV7 serotypes plus 1, 3, 5, 6A, 7F and 19A. PCV13 revealed the same safety profile as PCV7 in pediatric patients, that are the main target of conjugate vaccines licensure. Some trials showed a better antibody response in terms of quantity and quality in HIV + adults by using PCV7 as compared to PPV23. However these data were not unequivocally confirmed in further studies on the use of PCV7 alone or in combination with PPV23. The first trials of PCV13 use in adults showed the same or even better response compared to PPV23, with a safety and tolerability similar to PCV7. PCV13 in HIV+ adults is a promising candidate prophylactic measure for pneumococcal infections.

The purpose of this study is to evaluate serological response and prevalence of nasopharyngeal colonization by *S. pneumoniae* in HIV-positive non-hospitalized adults, following vaccination with one dose of PPV23, and in unvaccinated HIV-negative subjects.

To completion of the study “Serological Response to Antipneumococcal Vaccination and Impact on *Streptococcus Pneumoniae* Nasal Carriage in HIV Adults” (protocol code PCV13-HIV2011 EudraCT number 2011-004518-40) the present study will be conducted simultaneously, for a microbiological and serological monitoring in HIV-positive adults with previous PPV23 vaccination and in HIV-negative subjects, regardless their vaccination status. Correlation analyses between clinical-anamestic data, immune response and microbiological results and the comparison between the populations from the main study (EudraCT number 2011-004518-40 ; protocol code PCV13-HIV2011) and from this sub-study (protocol code PNEUMO-HIV 2011) will provide essential clinical and epidemiologic findings useful to choice the optimal therapy and prophylaxis to prevent the pneumococcal diseases in HIV-positive adults.

**Primary Outcome Measures:**

- Determine the rate of nasal colonization by different pneumococcal serotypes in HIV-positive and HIV-negative adults, in relation to baseline antibody titers at T0;
- Determine the basal serological response (qualitative and quantitative) in HIV-positive and HIV-negative adults;
- Define serological response after one dose of PPV23 vaccine in HIV+ adults;
- Evaluate the effect of one dose of PPV23 vaccine in terms of nasal pneumococcal carriage and occurrence of invasive pneumococcal diseases;

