**RATIONALE**

*S. pneumoniae* is frequently isolated from nasal swabs of healthy subjects, but it can also cause severe diseases (pneumonia, bacteraemia, meningitis and sepsis).HIV-infected subjects are more sensitive to invasive diseases and recurrent infection than the general population. Nasal carriage is the main pathogenetic feature for invasive disease: bacteraemia is more frequent in carriers, HIV+ patients are constantly colonized by the same pneumococcal strain and their nasopharyngeal isolates have features similar to subsequent invasive strains. A 23-valent polysaccharide vaccine (PPV23) has long been available and recommended in the HIV+ population as prophylaxis for invasive disease. Studies regarding efficacy of PPV23 in HIV+ are controversial and highlight that immune response induced by PPV23 in HIV+ is poor and an hyporesponsiveness to repeated polysaccaridic antigens stimulation can occur. Moreover, PPV23 seems not to affect pneumococcal carriage status and could lead to emergence of non-vaccine serotypes. The conjugation of pneumococcal capsular polysaccharides to carrier proteins results in an improved T-cell dependent immune response, characterized by increased antibody concentrations and induction of T and B memory cells, with a demonstrated higher efficacy in children. A heptavalent vaccine conjugated with diphtheria toxoid (PCV7) is approved in Europe since 2001 and is effective in reducing incidence of invasive disease by vaccine serotypes (4, 6B, 9V, 14, 18C, 19F, 23F), in both children and adults, due to effect of herd immunity. A PCV13 formulation has recently been developed, covering PCV7 serotypes plus 1, 3, 5, 6A, 7F and 19A. PCV13 revealed the same safety profile as PCV7 in pediatric patients, that are the main target of conjugate vaccines licensure. Some trials showed a better antibody response in terms of quantity and quality in HIV + adults by using PCV7 as compared to PPV23. However these data were not unequivocally confirmed in further studies on the use of PCV7 alone or in combination with PPV23. The first trials of PCV13 use in adults showed the same or even better response compared to PPV23, with a safety and tolerability similar to PCV7. PCV13 in HIV+ adults is a promising candidate prophylactic measure for pneumococcal infections.

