The purpose of this study is to evaluate serological response and prevalence of nasopharyngeal colonization by *S. pneumoniae* in HIV+ non-hospitalized adults, following vaccination with 2 doses of PCV13.

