**Primary Outcome Measures:**

- Define the serological response after 2 doses of PCV13 vaccine. Measure of serological response after 2 doses of PCV13 vaccine (booster dose after 8 weeks) in HIV+ adults.
- Determine the rate of nasopharyngeal colonization by different pneumococcal serotypes in HIV-positive adults, in relation to baseline antibody titers at T0

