**Sample size and study group selection**

Applying these criteria, 50 HIV-infected adult outpatients who had never been vaccinated with any pneumococcal vaccine will be prospectively enrolled at two Infectious Diseases Clinical Centers in Central Italy (University Division of Infectious Diseases in Siena and Institute of Clinical Infectious Diseases, Catholic University of the Sacred Heart in Rome). All subjects will be required to sign a written informed consent before enrolling in the study.

At baseline (day 0, time of first vaccine dose administration), demographic, clinical and laboratory characteristics will be collected by patients interview.

At baseline, the enrolled patients will received two doses of the 13-valent vaccine (PCV13 Prevenar13®, Wyeth Vaccines) eight weeks apart.

Follow-up visits will be scheduled at 8 (time of second PCV13 dose), 24 and 48 weeks. At baseline and at each visit clinical and anamnestic data from patients will be recorded; peripheral venous blood samples will be collected to assess humoral immune response against PCV13 serotype; nasopharyngeal swabs will be collected, in order to investigate the *S. pneumonia* presence. CD4+ T cell count and plasma HIV-RNA will be also monitored.

After each vaccine administration, short- (30 minutes), medium- (≤5 days) and long-term adverse reactions will be monitored.

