**Analysis of isolates from nasopharingeal swab**

All the isolated strains of S. pneumoniae will be collected and subdued to antibiotic susceptibility testing following CLSI guidelines (Kirby-bauer disk diffusion tests, MIC susceptibility testing), and results will be interpreted following CLSI breakpoints. Susceptibility to recently introduced antibiotics (tigecycline, linezolid, quinupristin-dalfopristin) will be assessed. Strains will be also serotyped using sera obtained from SSI (Statens Serum Institut).

S. pneumoniae isolates will also be subdued to genotypic analysis. Genomic DNA from a fresh colture will be extracted with High Pure PCR Template Preparation Kit (Roche), then a multiplex PCR reaction will be performed so to deduce capsular serotype, as indicated by CDC (<http://www.cdc.gov/streplab/downloads/pcr-oligonucleotide-primers.pdf>). Clonalty of isolates will also be assessed through multi locus sequence typing (MLST), amplifying and sequencing seven housekeeping genes (aroE, gdh, gki, recP, spi, xpt and ddl) as indicated by MLST website ([http://www.mlst.net](http://www.mlst.net/)). PCR products will be purified, sequenced and results compared to international databases (<http://spneumoniae.mlst.net/>), allowing identification of different Sequence Types (STs) or performing phylogenic analysis of different STs through eBURST open-source software ([http://eburst.mlst.net](http://eburst.mlst.net/)).

We will also focus on other features of S. pneumoniae, such as the evaluation of molecular and phenotypic features amid isolates retrieved from invasive diseases. Moreover, a selection of Penicillin resistant S. pneumoniae (PNSSP) will be made and comparison against PSSP will be performed trough:

- PCR amplification of

-- PCR amplification of pbp2b, pbp2x genes (and pbp1a for PRSP strains)

-- restriction fragments length polymorphisms (RFLP) through Diversity DatabaseTM, Bio-Rad, version 2.2.0 software.

[figure not shown]

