**Clinical follow-up**

Subjects will be considered colonized by S. pneumoniae with at least one positive nasopharingeal swab. Colonized patients will be followed for the next 12 months so to observe potential invasive infections. Potential simultaneous colonization by two or more serotypes will be highlighted through the analysis of isolated colonies.

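### The PPV23 carriage effect counts any serotype, and the main study's post-vaccination carriage aim has no defined outcome; both need vaccine-type and non-vaccine-type carriage per visit

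*Supplement*

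**What the plan says.** The Supplement holds two protocols, the main study (PCV13-HIV2011) and the sub-study (PNEUMO-HIV 2011).

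- **Vaccine-effect outcome.** Sub-study, Primary Outcome Measures: "Evaluate the effect of one dose of PPV23 vaccine in terms of nasal pneumococcal carriage and occurrence of invasive pneumococcal diseases". It names no serotype group, visit or comparator.
- **Definition of colonized.** Clinical follow-up, same text in both protocols: "Subjects will be considered colonized by S. pneumoniae with at least one positive nasopharingeal swab".
- **Analysis.** Statistic Analysis, both protocols, lists colonization as one of several variables for regression, with no split by serotype.
- **Replacement.** Rationale, both protocols: "PPV23 seems not to affect pneumococcal carriage status and could lead to emergence of non-vaccine serotypes".
- **Serotype-level outcome.** Each list of primary outcomes has one, linked to baseline titres. Main study: "Determine the rate of nasopharyngeal colonization by different pneumococcal serotypes in HIV-positive adults, in relation to baseline antibody titers at T0". Sub-study: "Determine the rate of nasal colonization by different pneumococcal serotypes in HIV-positive and HIV-negative adults, in relation to baseline antibody titers at T0".
- **Main-study purpose.** The statement after the Rationale concerns serological response and colonization "in HIV+ non-hospitalized adults, following vaccination with 2 doses of PCV13". Main study, Sample size and study group selection: "Follow-up visits will be scheduled at 8 (time of second PCV13 dose), 24 and 48 weeks", with swabs at baseline and at each visit.
- **Typing.** Analysis of isolates: "Strains will be also serotyped using sera obtained from SSI". A multiplex PCR is also used to deduce the capsular serotype.

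**The concern.** A vaccine acts directly only on the serotypes it contains. If non-vaccine serotypes fill the space, any-type carriage is the sum of a fall and a rise. The rationale raises this possibility for PPV23, yet the outcome meant to show the PPV23 effect cannot separate the two parts. A real fall in vaccine-type carriage could then appear as a small effect, no effect, or an increase.

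There is a related gap in the main study. Its purpose is colonization after vaccination, and its title, as cited in the sub-study's purpose statement, announces an impact on nasal carriage. Its only listed carriage outcome is tied to T0 titres, with no post-vaccination time point and no change from baseline. The sub-study lists a vaccine effect on carriage; the main study has no counterpart.

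The definition of colonized adds a third difficulty. One positive swab at any time suffices, so baseline and follow-up are pooled. A person positive at T0 stays colonized whatever happens later, and no before-after change can be read from that definition.

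**Working it through.** The plan gives no carriage rate, effect size, alpha, power or dropout, so there is no stated figure to reproduce. The rates below are assumptions chosen to show the mechanism.

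**1. Size of the distortion.** Let *v* and *w* be vaccine-type and non-vaccine-type carriage at T0 (no co-carriage, so they add), *e* the relative reduction in vaccine-type carriage, and *r* the share of the lost carriage that is replaced.

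- Vaccine-type after vaccination: v(1 − e)
- Non-vaccine-type after: w + r·e·v
- Change in any-type carriage: −e·v(1 − r)

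With v = 10%, w = 5%, e = 0.5:

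| r | Vaccine-type | Any-type | Any-type ratio |
|---|---|---|---|
| 0 | 10% → 5% | 15% → 10% | 0.67 |
| 0.5 | 10% → 5% | 15% → 12.5% | 0.83 |
| 1.0 | 10% → 5% | 15% → 15% | 1.00 |
| 1.5 | 10% → 5% | 15% → 17.5% | 1.17 |

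The vaccine-type ratio is 0.50 in every row.

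**2. Dilution without replacement.** With vaccine-type share s = v/(v + w) and r = 0, the any-type ratio is (1 − s) + 0.5s. For s = 0.3, 0.5 and 0.7 it is 0.85, 0.75 and 0.65, against 0.50.

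**3. Direction.** Any-type change = vaccine-type change + non-vaccine-type change. Replacement makes the second term zero or positive, so it can only push any-type change upwards. It masks or reverses a fall and cannot produce a false one.

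**4. Information.** Numbers per group for two-sided 0.05 and 80% power, using the two-proportion formula as an unpaired approximation, e = 0.5:

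| v, w | Vaccine-type | Any-type, r = 0 | Any-type, r = 0.5 |
|---|---|---|---|
| 5%, 5% | 906 | 2005 | 8535 |
| 10%, 5% | 435 | 686 | 2978 |
| 10%, 10% | 435 | 906 | 3826 |
| 20%, 10% | 199 | 294 | 1251 |

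The vaccine-type outcome needs fewer people in every row, despite having fewer events. With 50 against 50, power in the 10%, 5% case is about 16% for vaccine-type and 5% to 11% for any-type. Across v = 5% to 20%, vaccine-type power is 10% to 29%.

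**5. Precision with 50 people.** Expected vaccine-type carriers at v = 10% are 50 × 0.10 = 5 at T0 and 50 × 0.05 = 2.5 afterwards. Exact 95% limits are 3.3% to 21.8% for 5/50 and 0.5% to 13.7% for 2/50.

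**6. Pooling of swabs.** With 10% carriage at each of four swabs (T0, weeks 8, 24, 48), the proportion ever positive lies between 10% (same people throughout) and 1 − 0.9⁴ = 34.4% (independent swabs). The result reflects turnover and the number of swabs, not a change after vaccination.

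**The case against.** The strongest reply is that the data are already there. Every isolate is serotyped, simultaneous carriage of several serotypes is to be identified, and colonization by serotype is a listed primary outcome in both studies, so a shift in serotypes would be visible. This is right about measurement: the gap is an undefined outcome and analysis, not missing data. It does not close the gap, because the listed serotype outcome is tied to baseline titres and defines neither a vaccine-type group nor a change after vaccination.

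Second, T0 in the main-study outcome dates the titres, not necessarily the swabs, and the one-positive-swab rule may serve mainly to choose who is followed for invasive disease. Both readings are possible. Even so, the outcome has no time point, and no other definition of carriage is given.

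Third, these are pilot studies with 50 vaccinated people each, and power is low under either outcome. That stands, and is why estimates with intervals are the right output. A pilot estimate still needs the right target.

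A reader might infer more than the text supports:

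- *That the protocol expects replacement.* It says only that it could occur, and only of PPV23.
- *That replacement could imitate a vaccine benefit.* Step 3 excludes this. A false fall would more plausibly come from chance or drift over time, since HIV-negative subjects are seen only at baseline and give no concurrent control.
- *That any-type carriage cannot be compared between the studies.* It is the one measure defined identically in both.
- *That vaccine-type carriage should become the dependent variable in a regression of vaccine effect.* All HIV-positive participants within a study are assigned the same vaccine, so there is no within-study contrast, and a handful of events would not support such a model.

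**Conclusion.** The point holds as a fault of outcome definition that should be mended. The sub-study's vaccine-effect outcome and the definition of colonized in both studies count any serotype, and the main study does not carry its post-vaccination carriage purpose into a defined outcome although it collects the swabs.

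If vaccination halves vaccine-type carriage and vaccine types make up 30% to 70% of carriage, the any-type ratio is 0.85 to 0.65 without replacement, 1.00 with full replacement, and above 1 if replacement exceeds the loss. These sizes rest wholly on assumed rates, additive carriage and, for the sample sizes, an unpaired approximation. The direction of the distortion does not depend on the rates chosen. The change improves what is estimated; it does not make either study adequately powered.

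**What to change.** 1. **Sub-study, Primary Outcome Measures.** Define the carriage effect as the within-person change from T0 to weeks 8, 24 and 48 in carriage of PPV23 serotypes, with non-PPV23 carriage reported alongside and any-type carriage as supportive. List the 23 serotypes, which the protocol does not.
2. **Main study, Primary Outcome Measures.** Add the matching outcome for the 13 PCV13 serotypes at the same visits.
3. **Clinical follow-up, both protocols.** For the effect analysis, score carriage at each visit. The one-positive-swab rule can remain for selecting people for the 12-month follow-up.
4. **Statistic Analysis, both protocols.** Report paired differences with confidence intervals, and state that there is no concurrent control over time.
5. **Cross-study description.** Show carriage of the 12 shared serotypes next to any-type carriage. The sub-study's IgG section already separates these from 6A, but its list repeats 6B and should be corrected.
6. **Prior PPV23 in the sub-study.** The inclusion criteria call for HIV-positive people with PPV23 within five years, the exclusion criteria bar previous PPV23, and the sample-size section gives PPV23 at baseline. These sections must be reconciled before a change from T0 can be interpreted.

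The cost is text only, with no new samples or assays. The downside is fewer events in the vaccine-type outcome, and so intervals that are wider relative to the rate estimated.

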**STUDY DESIGN**

This is a phase III, prospective, multicenter, pilot controlled study enrolling HIV-infected outpatients, aged 18–65 years with CD4 counts ≥200 cells/µL, pneumococcal vaccine-naïve.

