**STUDY DESIGN**

This is a prospective, multicenter, pilot controlled study enrolling HIV-infected outpatients, aged 18–65 years with CD4 counts ≥200 cells/µL, previously vaccinated , and unvaccinated HIV-negative subjects as a control,

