**Sample size and study group selection**

Applying these criteria, 50 HIV-infected adult outpatients and 100 subjects HIV negative will be prospectively enrolled at two Infectious Diseases Clinical Centers in Central Italy (University Division of Infectious Diseases in Siena and Institute of Clinical Infectious Diseases, Catholic University of the Sacred Heart in Rome). All subjects will be required to sign a written informed consent before enrolling in the study.

At baseline, demographic, clinical and laboratory characteristics will be collected by patients interview.

At baseline, the enrolled HIV-positive patients will received one dose of the 23-valent vaccine (PPV 23); follow-up visits will be scheduled at 8 (time of second PCV13 dose), 24 and 48 weeks.

At baseline and at each visit clinical and anamnestic data from patients will be recorded; peripheral venous blood samples will be collected to assess humoral immune response against PPV23 serotype; nasopharyngeal swabs will be collected, in order to investigate the *S. pneumonia* presence. CD4+ T cell count and plasma HIV-RNA will be also monitored.

After each vaccine administration, short- (30 minutes), medium- (≤5 days) and long-term adverse reactions will be monitored.

Oppositely, HIV negative subjects will not receive any vaccination; only at baseline clinical and anamnestic data will be recorded; peripheral venous blood samples will be collected to assess humoral immune response against PPV23 serotype; nasopharyngeal swabs will be collected, in order to investigate the *S. pneumonia* presence.

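### The sub-study's primary outcome on the effect of one PPV23 dose on carriage and invasive disease has no unvaccinated HIV-positive group followed after baseline to measure it against

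*Supplement*

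**What the plan says.** **Sub-study protocol (PNEUMO-HIV 2011).**
- The fourth item under Primary Outcome Measures is to "Evaluate the effect of one dose of PPV23 vaccine in terms of nasal pneumococcal carriage", and the same item goes on to name invasive disease.
- Study Design names "unvaccinated HIV-negative subjects as a control".
- Sample size and study group selection gives PPV23 to all 50 HIV-positive patients at baseline, with visits at weeks 8, 24 and 48. For the 100 controls it says: "HIV negative subjects will not receive any vaccination; only at baseline clinical and anamnestic data will be recorded". Their blood sample and swab are described in that same baseline-only sentence.
- Statistic Analysis names chi-squared or Fisher tests for differences in proportions.

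**Main protocol (PCV13-HIV2011).**
- Study Design: "This is a phase III, prospective, multicenter, pilot controlled study enrolling HIV-infected outpatients".
- Sample size and study group selection describes one group: "50 HIV-infected adult outpatients who had never been vaccinated with any pneumococcal vaccine will be prospectively enrolled", and "the enrolled patients will received two doses of the 13-valent vaccine". The visits are the same, at weeks 8, 24 and 48.

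**Link between the two.** The sub-study's purpose statement says the studies run simultaneously and that their populations will be compared. Both Statistic Analysis sections announce further analyses using both sets of results, without saying which contrast, endpoint or adjustment is meant.

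**The concern.** The effect of a vaccine on carriage is the difference between what happens with it and what would have happened over the same weeks without it. Estimating that needs comparable people who go without the vaccine and are swabbed at the same times. If the design has none, the primary outcome promises something it cannot deliver. A fall or rise in carriage between baseline and week 24 could equally come from natural clearance and acquisition, season, or chance in a small count.

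This matters because it is a primary outcome, and because the sub-study's purpose statement says the findings are meant to inform the choice of prophylaxis in HIV-positive adults.

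**Working it through.** **1. Who is swabbed, and when**

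| Group | N | Vaccine in study | Baseline | Wk 8 | Wk 24 | Wk 48 |
|---|---|---|---|---|---|---|
| Main study, HIV-positive | 50 | PCV13, all | yes | yes | yes | yes |
| Sub-study, HIV-positive | 50 | PPV23, all | yes | yes | yes | yes |
| Sub-study, HIV-negative | 100 | none | yes | no | no | no |

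HIV-positive patients followed without vaccine: 0 of 50 + 50 = 100. Controls with a scheduled post-baseline swab: 0 of 100.

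**2. What each available comparison can show**
- *HIV-negative against HIV-positive at baseline:* carriage and serology by HIV status. This serves the first two sub-study primary outcomes.
- *Within the PPV23 group over time:* change from baseline, with no control for time.
- *PPV23 group against PCV13 group:* a relative contrast between two vaccines, not randomised. The main study is vaccine-naive, while the sub-study's purpose, design and inclusion text describe previously vaccinated patients.
- *PPV23 against no vaccine, weeks 8 to 48:* not available.

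**3. Is baseline free of PPV23?** The sub-study's purpose, Study Design and Inclusion Criteria describe HIV-positive patients with previous PPV23 (within 5 years in the Inclusion Criteria). Its Exclusion Criteria rule out previous PPV23. If the inclusion text governs, even the within-patient change is not one dose against none.

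**4. Invasive disease.** Clinical follow-up says colonised subjects are followed for 12 months for invasive infection. Read broadly, this could include HIV-negative carriers. It would still compare by HIV status and would add no swabs. With 0 events in 50 patients, the exact two-sided 95% upper limit is 1 − 0.025^(1/50) = 7.1%.

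**5. Illustrations.** The documents give no carriage rate, so per-swab rates of 5%, 10% and 20% are assumed. There is no sample-size calculation to reproduce.

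*(a) Unequal swab counts.* Colonised means at least one positive swab. With independent swabs, four swabs give 1 − (1 − p)^4; at 10% this is 1 − 0.6561 = 34.4%.

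*(b) Before-after in 50 patients, carriage halved, exact McNemar at two-sided 5%.* With independent occasions at 10%, the discordant probabilities are 0.10 × 0.95 = 0.095 and 0.05 × 0.90 = 0.045, so 50 × 0.14 = 7 discordant pairs are expected. With maximal correlation they are 0.05 and 0.

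*(c) PPV23 against PCV13, 50 v 50, one visit, carriage halved, two-sided 5%.*

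| Assumed carriage | (a) one swab / any of four | (b) power, independent / maximal correlation | (c) power; n per group for 80% |
|---|---|---|---|
| 5% | 5% / 18.5% | 1% / 0.2% | 10%; 906 |
| 10% | 10% / 34.4% | 7% / 4% | 16%; 435 |
| 20% | 20% / 59.0% | 20% / 38% | 29%; 199 |

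Column (a) is a worst case, since persistent carriage shrinks the gap. It shows why the HIV-negative group must not be compared with ever-colonised HIV-positive patients. Columns (b) and (c) show that neither remaining contrast would be precise.

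**The case against.** The best defence is the linked design. The two HIV-positive cohorts run at the same time, at the same two centres, on the same visits, and a comparison between them is planned. Each is therefore a concurrent, followed comparator for the other, and controlled has a weak external meaning for the main study. A reader might infer that the HIV-negative group is the only comparator in the plan; the documents do not support that. If the sub-study patients do have previous PPV23, their baseline swabs could also be set against those of the vaccine-naive main-study patients, a confounded cross-sectional contrast within HIV-positive adults. All of this stands, but none of it gives PPV23 against no vaccine over weeks 8 to 48.

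A reader might also infer that every before-after change would be reported as a vaccine effect. The plan does not say so. It names no before-after carriage analysis, and its Rationale suggests PPV23 does not affect carriage.

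Nor do the documents support a definite seasonal bias. Suppose 12% baseline carriage (6/50) and 1.5- to 2-fold higher carriage in winter. Summer carriage would then be 12%/1.5 = 8% (4/50) or 12%/2 = 6% (3/50), an apparent fall of 33% to 50%. Those inputs, and the front-loaded enrolment they need, are assumptions. For a 1 November start, week 24 is mid-April, week 8 is 27 December and week 48 is 2 October, so two of the three visits lie nearer the baseline season. Enrolment spread evenly over the year would cancel the effect. Fisher's test on these counts gives p = 0.74 and 0.49. Season is a possible explanation that the design cannot exclude, not a demonstrated error.

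Pilot status excuses small numbers. It does not supply a comparator for an outcome worded as an effect.

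**Conclusion.** The point holds in this form: the sub-study's fourth primary outcome is worded as a vaccine effect, and neither protocol follows an unvaccinated HIV-positive group that could show it. The declared control is valid for the baseline comparison by HIV status and for nothing later. The PPV23-versus-PCV13 comparison is real but non-randomised, confounded by prior vaccination as the eligibility text mostly reads, and unspecified in the plan.

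This conclusion rests only on the groups, treatments and visits stated in the protocols. It needs no assumed carriage rate; the assumed rates show only how imprecise the remaining contrasts would be. The label on the main study is a lesser matter, because its own primary outcomes make no claim of a vaccine effect on carriage.

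**What to change.** 1. Reword the fourth sub-study primary outcome as *change from baseline in carriage at weeks 8, 24 and 48, and occurrence of invasive disease, after PPV23 (uncontrolled, descriptive)*.
2. In the sub-study's Statistic Analysis, name a paired method for that change, such as exact McNemar, in place of unpaired chi-squared or Fisher.
3. In the sub-study's Study Design, limit the word control to the baseline comparison by HIV status.
4. In the main Study Design, replace controlled with *single-group, with a parallel non-randomised PPV23 cohort*.
5. State that a before-after change in carriage will not be attributed causally to vaccination, and that any PCV13-versus-PPV23 contrast is non-randomised. If that contrast is wanted, specify its endpoint, visit and adjustment in advance.
6. Require the date of each swab to be recorded (the protocols do not say that it is) and show carriage by calendar quarter as a supporting table.
7. Reconcile the sub-study's purpose, Study Design, Inclusion Criteria and Exclusion Criteria on prior PPV23. Do the same for the HIV-negative group, which is unvaccinated in Study Design but admitted whatever its vaccination status in the purpose and Inclusion Criteria.

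The cost is a wording amendment to both protocols, one date field and one table, with no extra patients or visits. The downside is a weaker, descriptive claim about carriage.
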